### Patient follow-up and study endpoints

During the hospital course, patients will be visited every day by a cardiologist. Performed physical examinations and vital signs will be recorded. We will monitor the patients during admission and any signs of arrhythmia, pulmonary emboli, and coronary artery injury will be evaluated and recorded. Blood samples are drawn for measurement of fasting blood sugar (FBS), complete cell blood count (CBC), urea and electrolytes, liver function tests (LFTs), creatine kinase, and cardiac troponin T- and C-reactive protein. An electrocardiogram (ECG) test is also taken. Before the first cell infusion, cardiac magnetic resonance (CMR) imaging and echocardiography will be done. After cell infusion, patients will be discharged from the hospital with a prescription for beta-blocker, angiotensin-converting enzyme (ACE) inhibitor, aldosterone antagonist, aspirin, ticagrelor, statin, and nitrate spray or tablets to take as required and cardiac rehabilitation program. Blood tests, an ECG, and physical exams are again done at the 10th day (at time of admission for second cell infusion), 3-month, and 6-month visits. At the last visit, echocardiography and CMR will be re-performed. All the tests will be recorded.

The improvement in LVEF after 6 months will be the primary efficacy endpoint for this study. Secondary endpoints will be the infarct size of the infarcted and salvaged myocardium at 6 months as assessed by CMR, changes in LV function, left ventricular mass (LVM) index, left ventricular end diastolic volume (LVEDV), left ventricular end systolic volume (LVESD), and global longitudinal strain (GLS) at 6 months as determined by echocardiography.

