### Cardiac MRI

CMR will be performed for each patient 3 days and 6 months after primary PCI. For evaluation of the ventricular function and volume of cine-CMR, and for determining the microvascular obstruction and size of the infarcted myocardium evaluation, delayed enhancement (DE)-CMR will be used. T2 imaging will be used to assess the myocardial salvage and infarct size. Optimization of myocardial nulling will be done by the inversion time. Images will be evaluated in a blinded way by an expert operator. Scar and edema volumes will be determined by manually tracing the endocardial and epicardial contours after semi-automated selection of the normal remote myocardium per slice.

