### Echocardiography

For evaluation of LV systolic function, echocardiography will be performed. By using wall motion score and Simpson’s rule, EF will be calculated. LV function will be evaluated on the day of hospitalization before cell infusion and 6 months after cell infusion to determine the changes in EF. GLS will be measured using automated formulas in standard views.

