### Adjudication of potential endpoints

All measurements will be evaluated and judged by an independent, blinded expert. In the case of poor recordings, the expert chooses whether the measurement has adequate quality to be used for endpoint assessment or not. Measurements of inadequate quality will not be used in the analysis as missing measurements. Potential major adverse cardiac events (MACE) will be evaluated by an independent, blinded safety committee. All laboratory data and adjudications will be finalized and moved into the computer database prior to unblinding study.

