### Statistical analysis

All data will remain anonymous before the analysis, which will be done by an independent, expert member of the department not involved in the trial. Based on the findings from previous meta-analysis, a 3% improvement in ejection fraction, as measured by CMR after 6 months, will be considered significant [26]. An intention-to-treat analysis will be performed. We will also analyze the baseline demographic and clinical characteristics for each arm of the study. Mean and standard deviation will be used for continuous variables, and categorical data will be shown by frequencies and percentages. One-way analysis of variance (ANOVA) will be used to perform comparisons of LVEF changes after 6 month (primary endpoint) and also other outcomes between the treatment arms regarding the followed by post hoc Tukey’s test for comparisons of the double-doses-infusion arm with single-dose-infusion group and placebo control-treated groups individually. Only cases with complete follow-up will enter the final analysis. Paired *t*-test will be performed for within-group comparisons. Estimated treatment effect will be reported with 95% CI. All *p* values will be two-sided. Safety events such as the incidence of MACE (death, recurrent AMI, ICD insertion, non-target vessel revascularization…) and serious adverse events (SAE) will be compared among the three arms, and Kaplan-Meier curves will be used to show the pattern of events during the 6-month follow-up. Using Cox’s proportional hazards model, statistical significance and 95% CIs will be reported.

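### A patient whose 6-month CMR is lost to an ICD drops out of the LVEF analysis, contrary to intention-to-treat, and no fallback is stated although a 6-month echo LVEF exists

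*Protocol article*

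**What the plan says.** All references are to the protocol article.

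- **Event.** Statistical analysis counts "MACE (death, recurrent AMI, ICD insertion, non-target vessel revascularization" among the safety events compared across arms, and "Kaplan-Meier curves will be used to show the pattern of events during the 6-month follow-up".
- **Endpoint.** Patient follow-up and study endpoints states "The improvement in LVEF after 6 months will be the primary efficacy endpoint for this study" and names no modality there. Statistical analysis says "a 3% improvement in ejection fraction, as measured by CMR after 6 months, will be considered significant". The Echocardiography section schedules echo before infusion and "6 months after cell infusion to determine the changes in EF".
- **Schedule.** Cardiac MRI states "CMR will be performed for each patient 3 days and 6 months after primary PCI", with no provision for a patient who has a device by then. Patient follow-up and study endpoints adds "At the last visit, echocardiography and CMR will be re-performed".
- **Missing values.** Adjudication of potential endpoints states "Measurements of inadequate quality will not be used in the analysis as missing measurements". Statistical analysis promises an intention-to-treat analysis and then restricts the final analysis to patients with complete follow-up.
- **Blinding.** Randomization and study blinding names only the outcome assessors as blinded. Under Intervention, controls receive conventional treatment alone.

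**The concern.** The plan foresees an event that can remove its own endpoint measurement, and its analysis rules then exclude the patient. That exclusion may not be random. Every patient enters with LVEF below 40%, and if devices go mainly to those whose LVEF stays low, the missing scans are concentrated among poor outcomes. A one-way ANOVA on the remaining patients cannot correct for this.

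If the cells raise LVEF, more control than cell patients would lose their scan. The control mean among scanned patients would rise and the treatment effect would be understated. Clinicians who know the arm and implant more readily in controls would add bias in the same direction. With 20 patients per arm, each lost patient is 5% of an arm.

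**Working it through.** **Inputs from the document.** Planned difference of 3 points per step (control to single dose, single to double), SD 1.3, 20 per group (Sample size determination). It gives no ICD rate, no implant criterion and no figure for scan loss, so there is no plan figure to reproduce on this point.

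**How far SD 1.3 can be relied on.** Put into the plan's own formula, n = 2 × 1.3² × (1.960 + 1.282)² / 3² = 3.95, so 4 per group. With 15% dropout, 4/0.85 = 4.7, so 5. The plan states 16 at that stage. That mismatch is a separate matter, but it is a reason to show larger SDs as well.

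**Assumptions.** The 6-month LVEF change is normal with means 0, 3 and 6. A device takes away the scan below a common threshold, set so that 5% to 20% of controls (1 to 4 of 20) lose it. The alternative SDs are 5 and 8.

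**Formula.** If a share p of an arm is lost from the lower tail, the mean of the remainder rises by SD × φ(z) / (1 − p), where z is the standard normal quantile of p. The shortfall in a contrast is the control rise minus the cell-arm rise.

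**Worked cases.**

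- SD 1.3, 10% of controls lost: control rise = 1.3 × 0.1755 / 0.90 = 0.25. The single-dose arm loses almost nobody, so 3.00 becomes 2.75.
- SD 8, 20% of controls lost: control rise = 8 × 0.280 / 0.80 = 2.80. The threshold is −0.842 × 8 = −6.73. In the single-dose arm z = (−6.73 − 3)/8 = −1.217, so 11.2% are lost and the rise is 8 × 0.190 / 0.888 = 1.71. The shortfall is 2.80 − 1.71 = 1.09, so 3.00 becomes 1.91.

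| Dependence on outcome | SD | Lost: control / single | Single − control (true 3) | Shortfall | Double − single (true 3) |
|---|---|---|---|---|---|
| Complete | 1.3 | 5% / 0% | 2.86 | 0.14 | 3.00 |
| Complete | 1.3 | 15% / 0% | 2.65 | 0.35 | 3.00 |
| Complete | 1.3 | 20% / 0.1% | 2.55 | 0.45 | 3.00 |
| Complete | 5 | 5% / 1.2% | 2.62 | 0.38 | 2.87 |
| Complete | 5 | 20% / 7.5% | 2.01 | 0.99 | 2.49 |
| Complete | 8 | 5% / 2.2% | 2.56 | 0.44 | 2.76 |
| Complete | 8 | 20% / 11.2% | 1.91 | 1.09 | 2.24 |
| Correlation 0.5 (simulated) | 5 | 5% / 2.6% | 2.88 | 0.12 | 2.93 |
| Correlation 0.5 (simulated) | 8 | 20% / 15.2% | 2.71 | 0.29 | 2.75 |

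For double dose against control (true 6), the SD 8, 20% case gives 4.15, a shortfall of 1.85 or 31%.

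**No treatment effect.** With equal means and a common threshold, p and the rise are the same in every arm and the contrast is not biased.

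**The case against.** Several points on the other side stand.

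- **An LVEF value need not be lost.** Echo is repeated at 6 months, the endpoint sentence names no modality, and the Echocardiography section uses echo for the change in EF. If echo is the primary measure, a lost CMR does not touch the primary endpoint. But no section lets echo replace a missing CMR, and the threshold sentence points to CMR.
- **The causal links are inferred.** A reader might infer that ICDs are expected, that they go to the patients with the worst LVEF, and that the arms will lose scans at different rates. The document only lists ICD insertion as a possible event. It gives no rate or criterion, and it also monitors arrhythmia, another possible route to a device. That an ICD can spoil CMR is general technical knowledge, not in the document, and not every device does so.
- **Large biases are easy to assume.** A reader might multiply a 5 to 15 percentage-point difference in ICD share by a deficit of 5 to 10 EF points and get 0.25 to 1.5 points, or 8% to 50% of the planned 3. Deficits of that size are about 4 to 8 times the planned SD (5/1.3 = 3.8; 10/1.3 = 7.7), so the plan's own figures do not support that range.
- **The adjudication rule covers poor recordings, not scans never taken.** This is correct. The complete-follow-up restriction does the rest, and a patient without a CMR value cannot enter an ANOVA of CMR change in any case.

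One objection does not succeed: that missing-data handling belongs in an analysis plan not shown. The article itself states the exclusion rule, and that rule conflicts with its intention-to-treat statement.

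**Conclusion.** The concern holds in a conditional form. If CMR is the primary modality, following the article as written drops a patient whose 6-month scan is lost to a device, and that departs from intention-to-treat.

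The contrast is biased only if ICD use follows low LVEF and, in addition, the treatment changes LVEF or implant decisions differ by arm. When the cells work, or controls receive devices more readily, the bias runs against the cells. Implant practice leaning the other way would push it in the opposite direction. With no effect and equal practice there is none.

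Per 3-point step, the shortfall is about 0.1 to 0.4 points (5% to 12%) at SD 1.3 with 5% to 15% of control scans lost. It is about 0.1 to 0.3 points at SD 5 to 8 with correlation 0.5. The most it reaches here is about 1.1 points (36%), at SD 8 with 20% control loss and complete dependence. These figures illustrate the mechanism and do not forecast it. They also treat every ICD patient as losing the scan, which overstates the loss.

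**What to change.** 1. **Name one primary LVEF modality** and use it consistently in Patient follow-up and study endpoints, Echocardiography and Statistical analysis.
2. **Replace the complete-case rule for LVEF in Statistical analysis.** If CMR is primary, a randomised patient whose 6-month CMR is missing or unreadable, including because of a device, stays in the analysis through a model or multiple imputation. It uses the 6-month echo LVEF with the baseline CMR and echo LVEF.
3. **Report by arm** how many patients are affected, and show the complete-case result as a sensitivity analysis.

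All these measurements are already scheduled, so no visit or scan is added. The cost is slightly more analysis and reliance on the relationship between echo and CMR LVEF. With 20 per arm, the model should be kept simple. Patients who die before 6 months have neither measurement, so this does not settle how they are handled.

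Moving the final CMR ahead of an implant is not a good substitute. It would measure a group selected on outcome earlier than everyone else.

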### Sample size determination

According to the objectives and type of the study and citing previous studies in this field, taking into account the 5% error, 90% power, 3% difference between placebo group and single dose injection group, and another 3% difference between single and double injection groups after the 6 month follow-up period and 1.3 standard deviation and 1:1:1 ratio, the sample size will be estimated in each group using the formula $$ n=\frac{2{s}^2{\left({z}_{1-\raisebox{1ex}{$\alpha $}\!\left/ \!\raisebox{-1ex}{$2$}\right.}+{z}_{1-\beta}\right)}^2}{{\left(\partial \right)}^2} $$ . Due to the length of the study and repeated measurements, using the formula $$ {n}^{\prime }=n\times \frac{1}{1-p} $$, and a drop of 15%, the sample size is decided 16 in each group. Finally, considering that in this study, three groups will be compared and according to the formula, $$ {n}^{\prime }=n\times \sqrt{k} $$, 20 subjects will be needed in each group, so a total of 60 patients will be selected. In the above formula, the values of *z* are constant and equal to 97.5th percentile and 80th percentile of the standard distribution. The ratio of people in the two groups and the effect size are the value divided by the standard deviation.

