### Randomization and study blinding

Patients will be randomized 1:1:1 to receive WJ-MSCs using permuted block randomization with block size 6. The outcome assessors will be blinded to the assignment (single-blind). The randomization process will be done by using a web-based randomization service.

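### With 20 patients per arm, the Cox model named for MACE and SAE gives no usable hazard ratio or Wald interval for an arm without events, and unreliable ones when events are few

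*Protocol article*

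**What the plan says.** The Statistical analysis section of the Protocol article lists the safety events as "MACE (death, recurrent AMI, ICD insertion, non-target vessel revascularization", leaving the list open-ended, and adds serious adverse events. These "will be compared among the three arms". Kaplan-Meier curves have a descriptive role: "Kaplan-Meier curves will be used to show the pattern of events during the 6-month follow-up". Inference comes from a Cox proportional hazards model, for which "statistical significance and 95% CIs will be reported". No method is named for sparse or absent events, and the type of confidence limit is not stated.

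The number of patients is fixed in Sample size determination: "20 subjects will be needed in each group, so a total of 60 patients will be selected". That number was derived from LVEF. The article states no rate, expected count or power for MACE or SAE.

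Two other statements bear on the point. The Statistical analysis section says that categorical data will be shown as frequencies and percentages. It also says "Only cases with complete follow-up will enter the final analysis", next to a statement that the analysis will be by intention to treat.

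**The concern.** A Cox model estimates a hazard ratio by comparing arms at the times when events occur. If an arm has no event, the partial likelihood keeps rising as that arm's log hazard ratio moves towards minus infinity, or as the other arms' log hazard ratios move towards plus infinity when the empty arm is the reference. No finite maximum exists. Software then stops at an arbitrary large value with a huge standard error, and a Wald interval built on these carries no information. With one or two events in an arm the estimate exists, but the normal approximation behind the Wald p value and interval is poor.

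What is at stake is the safety comparison for a repeated intracoronary infusion. A fit that fails at analysis forces an unplanned choice of method after the data are known. A very wide interval labelled non-significant tells the reader little about how much excess risk the data leave open.

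**Working it through.** **Inputs.** Three arms of 20 (Sample size determination; 1:1:1 in Randomization and study blinding). Follow-up is 6 months. The plan has no safety figure to reproduce, so the event rate p is an assumption, taken as equal in all arms and varied from 5% to 20%. The 20 per arm is taken as given; how it was derived from LVEF does not matter here. As a second case, the plan's 15% dropout leaves 20 × 0.85 = 17 per arm, which applies if the complete-follow-up rule extends to safety.

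**Step 1: an arm with no event.** For one arm, q = (1 − p)^n. For at least one of three arms, 1 − (1 − q)^3. Example at p = 5%, n = 20: q = 0.95^20 = 0.358, and 1 − 0.642^3 = 0.736.

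**Step 2: an arm with two or fewer events.** Let r = P(X ≤ 2) for X binomial(20, p). For at least one of three arms, 1 − (1 − r)^3. Example at p = 10%: r = 0.677, and 1 − 0.323^3 = 0.966.

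| Assumed 6-month rate | Expected events in 60 | Control arm empty (n = 20) | At least one arm empty (n = 20) | At least one arm empty (n = 17) | At least one arm with ≤ 2 events (n = 20) |
|---|---|---|---|---|---|
| 5% | 3 | 36% | 74% | 80% | over 99% |
| 10% | 6 | 12% | 32% | 42% | 97% |
| 15% | 9 | 4% | 11% | 18% | 79% |
| 20% | 12 | 1% | 3% | 7% | 50% |

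**Step 3: where an empty arm becomes more likely than not.** Setting 1 − (1 − q)^3 = 0.5 gives q = 0.206, so p = 1 − 0.206^(1/20) = 7.6% with 20 per arm, and 8.9% with 17.

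**Step 4: what the model returns.** An ordinary Cox fit to an invented data set with 2, 1 and 0 events in three arms of 20 gave, for the empty arm against the first arm, a log hazard ratio of about −30 with a standard error of about 2.2 million and a convergence warning. The Wald 95% interval therefore runs in effect from 0 to infinity. The other contrast remained estimable (log hazard ratio −0.71, SE 1.22). The profile-likelihood upper limit for the empty arm was finite, at a hazard ratio of 1.56.

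**Step 5: what few events give.** With 2 against 2 events, the rough approximation SE = √(1/2 + 1/2) = 1 gives a 95% interval for a hazard ratio of 1 of exp(±1.96), or about 0.14 to 7.1.

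**Step 6: the exact alternative.** For 0 of 20, the Clopper-Pearson 95% upper limit is 1 − 0.025^(1/20) = 16.8%, a finite and readable statement of what the data leave open.

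**The case against.** The strongest reply is that no event rate is given, so an empty arm cannot be called likely. Patients have an anterior STEMI with LVEF below 40%, the MACE list is open-ended, and SAE may be more frequent than MACE. The only event frequency in the article is heart failure in 14 to 36% of patients hospitalised for AMI (Background). That is not a MACE rate, but it lends no support to the low end. At 14%, the chance of an empty arm with 20 per arm is 14%. This stands: the empty-arm problem depends on the rate. It does not remove the sparse-event problem, since at 14% the chance that some arm has two or fewer events is still 84%.

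A reader might also infer that the Cox analysis would give no finite result at all. The documents do not support that. The article does not say that the limits will be Wald limits. Only contrasts with the empty arm fail, score and likelihood-ratio tests remain valid to compute, and a one-sided profile limit is finite. None of these is named, however, and Wald limits are the usual default.

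The plan already provides frequencies and percentages for categorical data, and the three-monthly DSMB tables give events by treatment group, though for monitoring. Part of the remedy is therefore in place; what is missing is an interval around those proportions.

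A sparse-event fallback might be left to an analysis plan that is not shown. That would answer a complaint about a missing detail. Here the article states a method, and the method suits the planned numbers poorly.

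Finally, a reader might infer that the trial intends to present non-significance as evidence of safety, or that Cox must give way to an exact test. The article does not say the first. The second is a trade-off, because an exact test on proportions ignores timing and censoring, and 15% dropout is expected.

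**Conclusion.** The point holds in a limited form. As stated, the plan relies on a Cox model for significance and 95% CIs on MACE and SAE with 20 patients per arm and names nothing for sparse events. For contrasts with an empty arm, an ordinary fit with Wald limits breaks down. How often this happens rests on an assumed rate that is equal across arms: 74% at 5%, falling to 3% at 20%, and above one half only below about 7.6%. The broader weakness, too few events for large-sample limits, covers most of the assumed range: the chance that some arm has two or fewer events falls below 79% only for rates above 15%, and is still 50% at 20%. If SAE or the final MACE composite is more frequent than 20%, the concern fades for that outcome. This is an inexpensive improvement to the safety analysis, which should be made but does not call the trial's main result into question.

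**What to change.** Revise the safety sentences in Statistical analysis along these lines:

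- Report the number and percentage of patients with MACE and with SAE in each arm, with exact (Clopper-Pearson) 95% CIs.
- Report pairwise risk differences with exact 95% CIs.
- Keep the Kaplan-Meier curves.
- If a hazard ratio is reported, use Firth-penalised Cox with profile-likelihood CIs in place of ordinary Cox with Wald limits.
- A Fisher-Freeman-Halton exact test across the three arms is optional.

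It would also help to state that a non-significant difference is not evidence of equal safety.

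The cost is a few lines of analysis text, with no new data and no change in sample size. Exact intervals are wide and slightly conservative, and exact proportions ignore event timing and censoring, which is a reason to keep the Kaplan-Meier curves beside them.

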### Adverse events reporting

The Executive Committee of the Study will report the case to an independent Data and Safety and Monitoring Board (DSMB) for monitoring the patient safety. The DSMB can suggest that the trial should be ceased early due to concerns about the patients’ safety or because the major research question has been answered. The DSMB will monitor the safety events all over the trial which will include unexpected SAEs, mortality, liposuction complications, intracoronary infusion complications, and serious or life-threatening arrhythmia. Every 3 months, DSMB statistician will report the patient safety events by tabulations for treatment groups. Mortalities are reported for every individual.

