### Intervention

The cGMP certified clinical-grad hWJ-MSCs produced by Cell Tech Pharmed Co. Ltd. (Tehran, Iran) are transported to the ward on the infusion day. The hWJ-MSCs were suspended in 0.9% normal saline. A qualified person will issue the certificate of analysis for each batch. The release of cells is in compliance with product specifications. The shipment will be handled considering validated standard operation protocols.

Forty patients in the two intervention arms will receive one intracoronary dose of 10^7^ WJ-MSCs infusion, and the control group will be administered only the conventional supportive treatment. For 20 patients among those who had received the first dose, the second dose of 10^7^ WJ-MSCs infusion was done within 10 days after the first injection.

A total of 60 patients in the three groups will be randomized in a 1:1:1 pattern to receive two doses of WJ-MSCs (*n* = 20; 2 × 10^7^ cells) or one dose of WJ-MSCs (*n* = 20; 1 × 10^7^ cells) in combination with conventional supportive treatments or conventional supportive treatments alone (*n* = 20).

When the cells are ready for infusion, the patients will return to the cardiac catheterization laboratory. The total number of 10^7^ WJ-MSCs will be infused via intracoronary route. If the activated clotting time is under 200, a weight-based bolus dose of heparin will be used.

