Therapeutic 6 Fr guiding catheter will be inserted into the left main artery. Two hundred micrograms of nitroglycerin will be infused via the guiding catheter. Angiography of LAD will be done, and TIMI flow will be documented. 0.014-inch soft-tipped guidewire wire will be inserted into LAD at distal edge of the stent. An over-the-wire balloon will be passed and placed within the stented area. It will be inflated to occlude the vessel. The guiding wire will be removed from the microinfusion device. Infusion syringe will be connected to the infusion catheter, and infusion of MSCs will be initiated at 2.5 ml/min. Occlusion with balloon catheter will be done using low pressure inflation (2–4 bar). Before each cell infusion, total occlusion of the coronary artery will be confirmed by injection of dye in the selected vessel. When one third volume of the cells is infused, the infusion pump will be ceased, and the contrast agent is injected into the guiding catheter to assess the TIMI coronary flow. This will be done again for the second one third volume. When cell infusion is completed, the coronary flow wire will be placed via the microinfusion catheter. After 10 days, this procedure will be repeated for patients in the third group.

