### Ethical considerations

All ethical considerations of this trial were discussed and approved in institutional review board of Shiraz University of Medical Sciences (IR.SUMS.REC.1399.406). Taking informed consent in the acute setting is an important ethical issue with this type of trial. To deal with this issue, we will obtain the consent forms when the patients are in a stable clinical condition and had sufficient time to recover from sedation or analgesics. Using the patients’ umbilical cord Wharton’s jelly tissue-derived MSCs will have the risk of an allergic reaction near zero. Furthermore, using a low balloon inflation pressure and a divided infusion time prevented intracoronary cell infusion complications.

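### The safety text does not fit this intervention: it monitors liposuction, attributes a manufactured cell product to the patients, and does not name target-vessel revascularisation in MACE

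*Protocol article*

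**What the plan says.** All references are to the protocol article.

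- **Adverse events reporting** gives the events the DSMB follows throughout the trial: unexpected SAEs and deaths, then "liposuction complications, intracoronary infusion complications, and serious or life-threatening arrhythmia".
- **Intervention** says the cells come from a named manufacturer and "are transported to the ward on the infusion day". On release it says: "A qualified person will issue the certificate of analysis for each batch".
- **Ethical considerations** attributes the umbilical cord source to the patients and states that these "tissue-derived MSCs will have the risk of an allergic reaction near zero".
- **Intervention** also describes the infusion in the LAD: "An over-the-wire balloon will be passed and placed within the stented area". The balloon is then inflated to occlude the vessel. The double-dose arm repeats the procedure.
- **Statistical analysis** illustrates MACE as "death, recurrent AMI, ICD insertion, non-target vessel revascularization", followed by an ellipsis. MACE and SAEs are compared among the three arms, with Kaplan-Meier curves and a Cox model.
- **Adjudication of potential endpoints** sends potential MACE to an independent, blinded safety committee.

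**The concern.** A safety list should name the harms that the intervention can plausibly cause. Here it names one that cannot occur and does not name reactions to the infused product. The ethics text sets the allergy risk aside on a statement about cell origin that another section contradicts.

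The MACE wording matters for the comparison between arms. The mechanical exposure is in the treated vessel and belongs to the cell arms only, yet the one kind of revascularisation named is in the other vessels. With the list left open, whether a repeat intervention on the LAD counts could be settled after events are known. That is undesirable for an adjudicated composite analysed by a Cox model.

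**Working it through.** The plan gives no figure to reproduce, so the check sets the sections side by side and counts exposure.

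**1. Liposuction.** The Intervention section takes the patient from arrival of the finished product to the end of the intracoronary infusion. Neither it nor the follow-up section includes any tissue harvest. The liposuction item can only return zero events.

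**2. Origin of the cells.** The Intervention section has a company produce the cells, a certificate issued per batch, and shipment to the ward. Eligible patients are aged 20 to 60, infusion follows an infarction 3 to 7 days old, and no step obtains a patient's own cord tissue. Ethical considerations nevertheless attributes the tissue to the patients. The two statements cannot both describe this product. The article does not call the trial product allogeneic; that it comes from donors is an inference from these facts.

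**3. Reactions to the product.** Comparing the five DSMB items with the intervention, hypersensitivity and immune reactions are not named. A serious reaction could enter as an unexpected SAE, and one during the procedure as an infusion complication. A non-serious reaction after the procedure has no evident category.

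**4. Exposure of the treated vessel, from the Intervention section.**

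| Arm | Patients | Planned infusions each | Infusions with LAD occlusion |
|---|---|---|---|
| Double dose | 20 | 2 | 20 × 2 = 40 |
| Single dose | 20 | 1 | 20 × 1 = 20 |
| Control | 20 | 0 | 0 |
| Total | 60 | | 60 |

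So 20 + 20 = 40 patients have the stented LAD occluded at least once, and 20 of them twice.

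**5. What the named MACE items would catch.** A treated-vessel problem that leads to infarction or death counts through those components. One that leads to an ICD also counts. A revascularisation of the LAD without any of these is not named, and only the ellipsis could admit it.

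**6. What the other safety provisions would catch.** SAEs are compared by arm, and the DSMB sees infusion complications. Each provision is narrower than inclusion in MACE:

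- The DSMB item covers unexpected SAEs, so an SAE classed as expected need not reach it by that route.
- Coronary artery injury is recorded during admission, while an LAD revascularisation could come later in the six months.
- The blinded committee is described for MACE, and SAEs are not mentioned there. Only outcome assessors are blinded in this trial, so an event outside MACE may lose that protection.

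**The case against.** The strongest reply is that these are wording defects with limited consequences. A reader might infer that the likeliest harms go uncounted. The text does not support that: death and recurrent AMI are in MACE, all SAEs are compared by arm, the DSMB follows infusion complications and serious arrhythmia, and coronary injury is recorded in hospital. The MACE list is introduced as an example, and a condensed article may leave the full definition to the full protocol. This stands, and it limits the point to target-vessel revascularisation that is not accompanied by another named component. It does not explain why the one revascularisation item that is spelled out excludes the treated vessel.

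A reader might also infer that the allergy statement has no basis. The Background gives one that does not depend on the patient's own cells: it describes MSCs as immune privileged and cites a trial as showing allogeneic cells to be safe. Whether that suffices can be argued. What remains is that the ethics section rests its statement on a different premise, which the Intervention section contradicts.

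Finally, the DSMB may suggest stopping "because the major research question has been answered", and a reader might infer unprotected interim efficacy testing and an inflated type I error. The article describes no interim efficacy test. The only regular DSMB report it mentions is a three-monthly tabulation of safety events, and any boundary could sit in an analysis plan or charter that is not shown. This forms no part of the point.

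**Conclusion.** The point holds in three limited parts. The DSMB list contains an event that cannot occur and does not name reactions to a product that 20 patients receive twice. The article contradicts itself on where the cells come from. The MACE list is open and does not name target-vessel revascularisation, although 40 patients, 20 of them twice, have the stented LAD occluded.

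The size can be given only as exposure, because the article states no expected event rates. The primary LVEF comparison is not affected. The risk is to the clarity and comparability of the safety results.

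Three assumptions matter:

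- Controls have no infusion procedure, as the Intervention section says. The abstract and the analysis section speak of placebo, and a sham infusion would weaken the contrast between arms.
- SAE carries its usual definition, which the article does not give.
- The cells come from donors, which is inferred.

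**What to change.** 1. In Adverse events reporting, replace the liposuction item with hypersensitivity or immune reactions to the cell product.
2. Reconcile Ethical considerations with Intervention on cell origin, and rest the allergy statement on whatever premise is then correct.
3. In Statistical analysis, remove the ellipsis and close the MACE list. Include any coronary revascularisation, reported separately for target and non-target vessel, and list stent thrombosis.

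The trial is recruiting, so the closed definition should be dated, fixed before unblinding, and applied by the blinded committee to events already recorded as well as to new ones.

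The cost is small edits to the protocol, the case report form and the DSMB wording, plus a check of patients already enrolled. Visits, sample size and treatment are unchanged.
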